**5.3.1. CRITERIA AND PROCEDURES FOR STOPPING PROCESSING / AND EXCLUSION**

- FINAL STOP: In case of a serious adverse reaction

- No prohibition to participate in another protocol

**5.3.2. DATA COLLECTION AND MONITORING PROCEDURES**

The follow-up visits will all take place at the Nancy Thermal site in the spa center. They will be carried out by the thermal physician and/or the assessor who will collect the data necessary for the study (V0, V1, V2, V3 and V4) (see monitoring table). The thermal physician also ensures the follow-up medical treatment and collects adverse reactions.

**5.3.3. REPLACEMENT OF PERSONS**

NA

**5.3.4 PROCEDURES FOR MONITORING PEOPLE**

NA

**5.4. RECRUITMENT PROCEDURES**

Information on the Nancy Thermal study will be provided to general practitioners and rheumatologists (mail and/or information meeting) in the months preceding the start of the study. Patient information will be provided through the press (regional press release and local radio stations), as well as by a poster campaign in the offices of physiotherapists, pharmacies, biological laboratories, and in the waiting rooms of general practitioners and rheumatologists. A call centre will be set up to plan appointments with investigating physicians.

Patients, informed by press and poster and wishing to participate, will make an appointment by telephone with the call centre (toll-free number put into service in December 2011). This first date will correspond to their selection visit. General practitioners and rheumatologists informed by letter/information meetings may refer their patient via the call centre.

**6. INTERVENTION**

6.1. Care protocol

"Classical spa therapy".

The care protocol strictly follows the one recently validated in the "Thermarthrosis" study[1], i.e., 4 thermal treatments per day, 6 days a week for 3 weeks (18 sessions in total).

The 4 thermal treatments are (1) water jet at 37°C for 15 min in individual sessions; (2) massages under jet at 38°C by physiotherapist for 10 min, (3) Illutations (sludge applications) at 45°C for 15 min, (4) mobilization in the pool at 32°C in collective sessions (groups of 6) for 25 min.

"Active spa therapy"

This cure combines successively 3 weeks of thermal treatments according to the Thermarthrosis scheme (4 cares/sessions) but at the rate of 3 sessions per week (9 sessions) then 3 weeks of rehabilitation/active physiotherapy at 3 sessions per week (9 sessions) for a total of 6 weeks and a total of 18 sessions.

This approach aims to meet the following objectives: to prolong the indolence acquired in phase 1, to improve joint mobility and muscle function, improve proprioception and develop appropriate attitudes and behaviour. Indeed, after a rest phase, it seems logical to recondition the patient for effort by correcting proprioceptive disorders and muscle deficiencies to prolong the long-term effectiveness of the spa treatment. However, no study has so far assessed the value of combining a phase of sedation provided by thermal treatments with an active approach of muscle strengthening and proprioceptive work in knee OA.

The first phase of active spa therapy includes the 4 treatments of classic spa therapy at the rate of 3 sessions per week for 3 weeks, i.e,. 9 sessions: waterjet at 37°C for 15 min in these individual sessions, massages under jet at 38°C by physiotherapist for 10 min, illutations (sludge applications) at 45°C for 15 min and mobilization in the pool at 32°C in group sessions (groups of 6) for 25 min [1].

The second phase of care was defined in collaboration with [name], and the persons in charge of the School of Physiotherapy, [name] and [name]. Practical care will be provided by students in massage and physiotherapy under the supervision of a qualified professional physiotherapist. It will take place over 3 weeks at the rate of 3 sessions per week, or 9 sessions.

Rehabilitation care will include the following:

1) preparatory work by the lower limbs based on local hot physiotherapy ("hot pac"), the participant being in a strict supine position with cushions under the head and under the popliteal cavity of the non-massaged knee, and manual massages with effleurage of the lower limb, sliding pressure or static pressure stepped from the root of the lower limb to the foot and back for deep and superficial venous system, maneuvers relaxing thigh, calf and foot muscles followed by circulating sliding pressures. This treatment can be completed with palpating-rolling in the peri-articular region of the knee and a global effleurage for a total duration of 20 min;

2) a personalized work consisting of musculo-tendinous stretching adapted to the initial assessment, carried out in stages or continuously, manually or by posture, followed by muscle strengthening, preferably static or in a chain, always adapted to the initial assessment and carried out against manual resistance, of the diagonal spiral Kabat type, or instrumental resistance, of the elastic, analytical or global resistance type;

3) global work, proprioceptive and functional, consisting of tests and eye balance exercises with eyes open and closed, on a Satel or Biorescue rehabilitation platform and on carpets and locomotion work on standardised walking paths;

4) a group educational session according to a predefined program with information about the disease, drug and non-drug OA management, risk factors (activities and weight), footwear and technical aids, lifestyle advice and exercises to be done at home and the hand-delivery of a follow-up booklet.

In the middle of the course, these sessions will be based on question-and-answer questionnaires, learning self-exercises and learning attitudes and gestures to be practiced in high-risk situations. At the end of the cure, these sessions will be conducted to self-correct exercises and gestures as well as the implementation of a physical activity program to be continued.

Physiotherapy care will be individualized and adapted (type and intensity of the exercises) to the initial physiotherapy assessment according to the recommendations of SOFCOT (Society for Orthopaedic Surgery) and SOFMER (Society of Medicine and Rehabilitation) from 2007.

Course of the spa therapy

The spa therapy will be carried out in the round pool, [name]. A space devoted to this study has been fully brought up to standard by the company “Thermes experts/ EUROSPA”. This space includes a reception area, a waiting room, a personal room, a medical office, a cloakroom for individuals taking the waters, a relaxation room, a physiotherapy and rehabilitation room, 2 shower rooms, 2 bathrooms, 2 affusion rooms, a water jet cabin, a hygiene plant, a sludge manufacturing room, a laboratory room, toilets and a laundry room.

A request for provisional approval of the use of water and premises for thermal care will be deposited with the Academy of Medicine after authorization from the AFSSA (stable bacteriological and chemical samples for a period of 12 consecutive months: in progress since December 2010) and the Prefect of the department of Meurthe et Moselle.

The chemical qualities of sodium chloride water are identical to those of the thermal spa of Amnéville les Thermes.

Spa therapy will be provided by physiotherapist professionals of spa and physiotherapy/rehabilitation care. They will be responsible for carrying out care, supervising care and monitoring tolerance and compliance with treatment. A training session will be provided prior to the start of the study to standardize practices.

The thermal physician will be in charge of examining the treatment to patients before the spa therapy, during the course of spa therapy and at the end of the spa therapy to ensure that it runs smoothly. The patients will continue their usual treatment.

**6.4. METHOD OF MONITORING COMPLIANCE**

The number of treatments actually performed by patients will also be recorded by the thermal doctor

**7. EFFECTIVENESS EVALUATION**

**7.1. DESCRIPTION OF THE PARAMETERS FOR EVALUATING EFFECTIVENESS**

Main Criterion

# The MCII in OA was determined by Tubach et al. [2]. The MCII is a threshold for improvement that is particularly suitable for therapeutic trials and takes into account that the MCID may be different for an improvement or a worsening. A patient is considered improved if the WOMAC index function subscale score is improved by at least 9.1 from the initial value and/or if the current pain measured on a VAS is improved by at least 19.9 mm. These values correspond to the smallest clinically relevant change for these two outcome criteria [2]. Improvements below this value will be considered treatment failures. Patients with improvement but would still need to have surgery during the study period will also be considered failures. The effect of the two types of spa therapy ("standard spa therapy" and "active spa therapy") for symptomatic knee OA will be assessed by proportion of patients who achieve a composite criterion combining the MCII for pain and/or functional abilities and the absence of knee surgery of the target knee at 6 months.

Secondary criteria

- Percentage of patients reaching the MCII (pain, function and composite score) at the end of the treatment and at 3 months
- Percentage of patients reaching the PASS (pain and function) at 3 and 6 months [14]. The PASS is the value beyond which the patient considers himself/herself to be well. It is defined as for the MCII by the 75th percentile of the score among patients whose assessment of the acceptable symptom state was “good” on a Likert scale with 5 answer modalities. The PASS for WOMAC function is 31 mm and for VAS for pain is 32 mm [14].
- Evolution of quality of life scores (Osteoarthritis Knee and hip Quality of life [OAKHQOL], SF-36) at 3 and 6 months
- Evolution of VAS-fatigue, VAS-pain at 3 and 6 months
- Evolution of WOMAC scores (function) at 3 and 6 months
- Patient satisfaction (overall VAS or heiQ module 9) at 3 and 6 months
- Evolution of drug and care consumption, use of surgery
- 6-minute walking test [43]
- Evolution of posturography parameters: modification of the length travelled and/or the area covered by the pressure centre of the feet after removal or disruption of sensory inputs, somesthesics of balance in distorted visual situations and static and dynamic positions [4]
- Adverse reactions

**7.2. METHODS AND SCHEDULE FOR MEASURING, COLLECTING AND ANALYSING THE PARAMETERS FOR EVALUATING EFFECTIVENESS.**

Clinical and perceived health data will be collected before the cure (V0), at 3 weeks (V1: end of the classic spa therapy or change of type of care for active spa therapy), at 6 weeks (V2: end of active spa therapy), at 3 months (V3: M3) and 6 months (V4: M6) and will include the following examinations: clinical exam (knee effusion, joint amplitudes), VAS-pain, VAS-fatigue, WOMAC, OAKHQOL, SF-36, satisfaction, drug consumption, total replacement surgery, side effects, posturography examination, 6-minute walking test. The number of spa care actually performed by the patients will also be listed (see follow-up table).

**8. SAFETY ASSESSMENT:**

**8.1. DESCRIPTION OF THE SECURITY ASSESSMENT PARAMETERS**

Adverse reactions that can be experienced with the spa therapy are rare, most often minor and transient. They are traditionally observed during the period of the spa therapy and are then part of what is usually called the "thermal crisis": tiredness, waking up of some of the usual pain, unusual sweating and insomnia. These effects rarely require the cessation of spa therapy. More serious health problems are possible but remain exceptional: heart problems, bacterial infections that may be present in warm waters (including Legionella infection).

Adverse reactions are noted at each follow-up visit.

No systematic biological or imaging monitoring of secondary effects is necessary.

**8.2. METHODS AND SCHEDULE FOR MEASURING, COLLECTING AND REPORTING THE SECURITY ASSESSMENT PARAMETERS**

The health care professionals performing spa therapy and the thermal physician are empowered to supervise patients as part of the management of the spa therapy.

Adverse reactions are noted at each follow-up visit.

Emergency contact information will be provided to patients:

[name],

Rheumatology Department

Nancy University Hospital, Brabois Hospitals;

[contact],

[contact],

[[contact]](mailto:[contact])

**8.3 PROCEDURES IN PLACE FOR THE REGISTRATION AND NOTIFICATION OF ADVERSE EVENTS**

**8-3-1 Definitions**

An adverse event is a harmful event that occurs in a person who is engaged in biomedical research, whether this person is related or not to the research or product to which this research relates.

An adverse reaction is a harmful and unintended reaction to an experimental drug, occurring at the normal dosage used in humans.

A serious adverse event (SAE) or serious adverse reaction is an event or effect that may have contributed to the patient's death, life-threatening event, hospitalization or prolongation of hospitalization, incapacity or significant disability, or lasting disability, or result in a congenital anomaly or malformation.

The list of expected adverse events related to the study is based on of the registration document.

An SAE is unexpected when it is not on this list.

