**Table: Follow-up**

|  | **Selection inclusion** | **V0** | **V1**  **3** weeks | **V2**  **6** weeks | **V3**  **3 months** | **V4**  **6 months** |
| --- | --- | --- | --- | --- | --- | --- |
| Inclusion  Zelen randomization  Consent | X  X  X |  |  |  |  |  |
|  |  |  |  |  |  |  |
|  |  |  |  |  |  |  |
| Sociodemographic data | X |  |  |  |  |  |
| History of OA | X |  |  |  |  |  |
| Clinical examination | X |  |  |  |  |  |
| X-ray | X |  |  |  |  |  |
| Ultrasonography | X |  |  |  |  |  |
| Treatment | X | X | X | X | X | X |
| VAS pain | X | X | X | X | X | X |
| Clinical follow-up |  | X | X | X | X | X |
| WOMAC |  | X | X | X | X | X |
| Quality of life |  | X | X | X | X | X |
| Posturography |  | X | X | X | X | X |
| 6-minute walking test |  | X | X | X | X | X |
| Care consumption |  | X | X | X | X | X |
| Adverse reactions |  |  | X | X | X | X |
| Satisfaction, heiQ |  |  | X | X | X | X |

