**4.4. EXPERIMENTAL DRUGS / MEDICAL TREATMENTS UNDER STUDY**

NA

**4.5. EXPECTED DURATION OF PARTICIPATION OF PERSONS AND DESCRIPTION OF THE CHRONOLOGY AND DURATION OF ALL TRIAL PERIODS, INCLUDING FOLLOW-UP, IF NECESSARY.**

Inclusion visit

The investigating physician verifies that the patient meets the inclusion criteria defined in advance, during a consultation carried out in the rheumatology department of Nancy University Hospital, Vandoeuvre les Nancy.

This physician will ensure that the patient has a knee X-ray performed according to current recommendations to verify the eligibility criteria. If necessary, a digitized radiograph will be taken in the rheumatology department.

After randomization, the investigating physician gives the eligible patient the information form that corresponds to the type of cure selected and obtains his/her consent to enter the study.

A plan is given to the patient.

Follow-up visits

Subsequent visits will all take place at the Nancy Thermal site in the spa center. They will involve the thermal physician and/or the assessor who will collect the data necessary for the study (V0, V1, V2, V3 and V4) (see monitoring table). The thermal physician also ensures the medical follow-up of the treatment and collects adverse reactions.

Occupancy, group planning:

This study will be conducted from mid-March to mid-December 2012. The flow of patients has been planned for both types of treatment: "classic spa therapy", “active spa therapy". A subgroup will consist of a maximum of 8 patients. Over 6 weeks and for each type of spa therapy, 4 subgroups can be included, i.e., 32 patients randomized in each group (64 patients). The study will focus on 5 cycles of 6 weeks for a total time of 30 weeks.

In the morning, the premises, care and carers will be dedicated to the "classic spa therapy" group, i.e., a daily occupation over 3 consecutive weeks for 2 subgroups of patients or over 6 weeks for 4 subgroups of patients.

In the afternoon, the premises, care and carers will be dedicated to the group “active spa therapy" for 3 weeks of usual spa therapy, then 3 weeks of rehabilitation/education by alternating sub-groups on alternate days, i.e., a daily occupation over 6 weeks for 4 subgroups.

This organization will allow for the same premises for both groups ("classic spa therapy" and “active spa therapy") while avoiding that they are in close contact, comparing their care while avoiding shifting the groups over time.

Coordination

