**8-3-4 Transmission of SAE**

As soon as an investigator becomes aware of a SAE or a new event, he/she shall declare this without delay to the promoter by faxing the SAE declaration form at [name].

- If it is an unexpected serious adverse reaction or a event, the sponsor will contact the investigator to write a report, which will be forwarded to the AFSSaPS, CPP and EUDRAVIGILANCE within 7 days in the event of death or vital prognosis, if not within 15 days.

When the event is not resolved on the date the fax is sent, the investigator is required to send a supplementary report to document the evolution or update missing data.

- An expected SAE will be collected by the sponsor for the preparation of annual safety reports.

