**8-3-5 Transmission of non-serious adverse reactions**

These will be briefly described by the investigator on the summary sheet dedicated to this end.

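### Adverse reactions are defined by reference to a drug the trial does not have, and non-serious harms are recorded only when judged to be reactions

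*Protocol*

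**What the plan says.** Section 8-3-1 defines two terms. The broad one begins "An adverse event is a harmful event that occurs in a person who is engaged in biomedical research" and goes on to include events unrelated to the research. The narrow one is: "An adverse reaction is a harmful and unintended reaction to an experimental drug, occurring at the normal dosage used in humans".

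Section 4.4, headed "EXPERIMENTAL DRUGS / MEDICAL TREATMENTS UNDER STUDY", is answered NA. So is section 4.6, on accounting for experimental medicinal products. Section 6.1 describes the interventions as spa sessions and, in the active arm, rehabilitation sessions.

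The safety data are specified with the narrow term:
- Adverse reactions are the last secondary criterion in the summary and in sections 4.1, 4.8 and 7.1.
- The safety row of the follow-up table (sections 4.2 and 4.5) is "Adverse reactions | | | X | X | X | X", that is, V1 to V4. There is no row for adverse events.
- Sections 8.1 and 8.2 say: "Adverse reactions are noted at each follow-up visit".
- The only route for non-serious harms is section 8-3-5, "Transmission of non-serious adverse reactions".
- Section 5.3.1 reads: "FINAL STOP: In case of a serious adverse reaction".

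The lists of visit data in sections 4.2 and 7.2 speak of side effects, which also implies a cause.

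**The concern.** A definition tied to a drug cannot be applied as written in a trial of spa and exercise sessions. Staff must set it aside and use some notion of harm caused by the cure. The term then works as a filter: a harmful but non-serious event enters the database only after someone has judged it to be treatment-related. The wider category, adverse events of any cause, is defined in 8-3-1, but no visit procedure collects it for non-serious events.

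Filtering before recording matters when the filter can work differently in the two arms. Here the arms differ in content, duration and timing, and patients know what they receive. The trial is meant to support an alternative cure presented as less tiring, and to support thermal approval of the site, so the comparison of tolerance will be read. Events that were never written down cannot be restored by a later analysis plan.

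**Working it through.** No figure in the Protocol depends on this point, so there is nothing to recompute. The check is to set the sections side by side.

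**1. Is the term used consistently?** Section 8-3-1 requires an experimental drug at normal dosage. Sections 4.4 and 4.6 say none is involved. Sections 8.1 and 8-3-3-3 nevertheless describe adverse reactions to spa therapy: tiredness, return of usual pain, sweating, insomnia and, exceptionally, cardiac problems or infection. The definition and these two sections cannot both stand.

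**2. What is collected, and under which term?**

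| Type of harm | Collected through | Causal judgement needed? |
|---|---|---|
| Serious, any cause | 8-3-4, declared to the sponsor on awareness | No |
| Non-serious, judged a reaction | V1–V4 row, 8.1, 8.2, 8-3-5 | Yes |
| Non-serious, not judged a reaction | No route as an adverse event | Not recorded as such |

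The third row is the gap.

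**3. Can the judgement differ by arm?** Three features of the design allow it.
- *Duration.* Standard therapy ends at week 3 and active therapy at week 6 (sections 4.2 and 7.2). Section 8.1 says reactions are traditionally seen during the period of therapy. A minor complaint at week 5 falls on treatment in the active arm and 5 − 3 = 2 weeks after the end of treatment in the standard arm. The same complaint could be attributed in one arm and dismissed in the other.
- *Blinding.* Section 4.3 says patients cannot be blinded, and states assessor blinding only for months 3 and 6. Nothing is stated for the 3- and 6-week visits, which close the treatment periods.
- *Collector.* Sections 4.5 and 5.3.2 give the collection of reactions to the thermal physician, who also follows the treatment. That this physician knows the arm is an inference from that role and from the separate morning and afternoon sessions. The Protocol does not state it.

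**4. Are harms of the rehabilitation phase described?** The active arm has 3 × 3 = 9 spa sessions and 3 × 3 = 9 rehabilitation sessions, so 9 of 18 are strengthening, proprioceptive and functional work. Sections 8.1 and 8-3-3-3 list nothing specific to that work. Staff asked to decide whether a minor event is a reaction to it have no description to go by.

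**5. What is captured elsewhere without a causal filter?** VAS pain, VAS fatigue, WOMAC, effusion, joint mobility, drug use and surgery are collected from V0 to V4 in both arms (sections 4.2 and 7.2), and care consumption is in the follow-up table. A persisting knee flare or marked tiredness would show there. A fall or strain that leaves no lasting symptom might not.

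**The case against.** The strongest reply is that the definition is a wording slip and that the Protocol, read as a whole, makes its meaning plain. Much of that stands.

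- A reader might infer that the safety criterion is empty because no event can meet a drug-based definition. The documents do not support this. Sections 8.1 and 8-3-3-3 show that reactions to the cure are meant, so the defect is a contradiction between sections.
- A reader might infer that serious-event reporting fails as well. It does not. Section 8-3-1 defines a serious adverse event or reaction as an event or effect, without mentioning a drug. Section 8-3-4 has investigators declare serious events on awareness, and its onward reporting opens "If it is an unexpected serious adverse reaction or a event", so it is not limited to reactions. A serious event missing from the expected list counts as unexpected and takes the faster route. The stop criterion in 5.3.1 is covered by the same definition of seriousness; its wording only has to agree with whatever definition is adopted.
- Pain, function and fatigue are measured in their own right, so the claim that the cure is less tiring does not rest on attributed reactions.
- It would be too strong to say that attribution is unblinded throughout. The assessor is blinded at months 3 and 6. The budget in section 13 places the thermal physician's data collection at V0 and V1 and a research nurse at 6 weeks, 3 months and 6 months.
- Adverse reactions are one secondary criterion, and the primary comparison does not use them.

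The reply leaves the filter in place. Even on the intended meaning, a non-serious event not judged causal has no route into the data as an adverse event, whoever collects it, and the unequal treatment periods remain.

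**Conclusion.** The point holds as a contradiction of definitions together with a gap in the recording of non-serious harms. It should be fixed, but it does not threaten the trial's main conclusion: the composite criterion, the margin, the sample size and the non-inferiority decision are untouched.

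Its size cannot be stated. The Protocol gives no expected event rate and no attribution rate, so any numerical difference between arms would be invented. The direction is also unknown: longer treatment in the active arm could inflate attributed events there, while the lack of any described rehabilitation harms could reduce them. The conclusion assumes that staff record what the visit table and sections 8.1 to 8-3-5 name, and that the case report form does not already ask for all events. The form is not among the documents.

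**What to change.** 1. In 8-3-1, define an adverse reaction as a harmful and unintended response to any study intervention or procedure: a spa session, a rehabilitation session or a study test. This removes the conflict with 8.1 and 8-3-3-3.
2. In both copies of the follow-up table and in 8.1, 8.2 and 8-3-5, record all adverse events at V1 to V4 in both arms whatever their cause. Make relation to treatment a separate field, completed after the event is entered.
3. Bring the secondary criterion and the side-effects item in the visit lists into line. Report all events by arm first and treatment-related events second.
4. Reconcile the wording of 5.3.1 with the revised definition without altering its clinical content.

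The visits and collectors already exist. The cost is Protocol wording and one case report form field, with somewhat more recording and higher reported event counts than a reactions-only list would give.
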